## Abstract

**Background:**

Mental health and sleep problems are highly prevalent among sedentary young women and substantially impair their well-being. Resistance training has shown promise in improving mental health and sleep outcomes. However, traditional set structures often induce high levels of fatigue and perceived exertion, which may reduce exercise tolerability and compromise sustained participation. By redistributing rest within sets, cluster-set resistance training may attenuate fatigue while preserving comparable training stimuli, thereby potentially enhancing benefits for mental health and sleep.

**Methods:**

This single-blind, parallel-group randomized controlled trial will recruit sedentary female college students. Participants will be randomly allocated (1:1:1) to (1) a non-exercising control group (CON), (2) traditional resistance training (TR), or (3) cluster-set resistance training (CS). The intervention will last 8 weeks (3 supervised sessions/week for TR and CS). Training exercises, weekly load progression, and total rest time per exercise will be identical between TR and CS; only set structure and the distribution of rest intervals will differ. Outcomes will be assessed at baseline, week 4, and week 8. The co-primary outcomes are DASS-21 total score and PSQI global score. Secondary outcomes include POMS total mood disturbance, actigraphy-derived sleep parameters, maximal dynamic strength, anthropometrics and body composition, and blood biomarkers (high-sensitivity C-reactive protein, cortisol, and serotonin).

**Discussion:**

This trial will evaluate whether TR and CS improve mental health and sleep compared with CON, and whether rest-redistribution cluster sets provide additional benefits over traditional set structures under comparable overall training stimuli. The findings may inform the design of future supervised resistance-training interventions and longer-term trials for sedentary young women.

**Clinical trial registration:**

This trial was registered at the China Clinical Trials Registration Center (www.chictr.org.cn), registration number is ChiCTR2500110077.

## Introduction

1

Mental health problems are a major public-health concern in university populations. The university years coincide with a peak period for the onset of common mental disorders, and cross-national data indicate that roughly one-third of first-year students screen positive for at least one diagnostic and statistical manual of mental disorders mood, anxiety, or substance use disorder (Auerbach et al., 2018). Depressive symptoms are also highly prevalent among university students, including Chinese university students (Ibrahim et al., 2013; Lei et al., 2016). Sleep problems represent another highly prevalent and clinically important concern; a recent meta-analysis estimated that nearly half of undergraduate students experience insomnia symptoms (Spyridonidis et al., 2025). Importantly, mental health and sleep should not be viewed as isolated outcomes. Psychological distress can impair sleep, whereas insomnia and related sleep disturbances increase the risk of subsequent mental disorders, supporting a bidirectional relationship between the two domains (Lo Martire et al., 2020; Hertenstein et al., 2019; Baglioni et al., 2011). Together, poor mental health and disturbed sleep can compromise emotional functioning, daily performance, academic engagement, and overall well-being (Nissen et al., 2021). These concerns are particularly relevant to sedentary young women for several reasons. First, women generally show a higher burden of depressive symptoms and insomnia than men, making psychological distress and sleep disturbance especially salient outcomes in female samples (Salk et al., 2017; Zhang and Wing, 2006). Moreover, in young women, menstrual-related symptoms and hormonal fluctuations may contribute to variability in mood and sleep, which highlights the need for careful assessment standardization (Baker and Driver, 2007). Additionally, prolonged sedentary behavior is common among female college students and is associated with poorer mental health and sleep outcomes (Zhang et al., 2022). Therefore, sedentary young women represent a focused and clinically meaningful subgroup for testing feasible exercise-based interventions.

Exercise is increasingly recognized as a promising non-pharmacological strategy for improving both mental health and sleep. Accumulating evidence suggests that regular physical activity can reduce symptoms of anxiety and depression and can also improve subjective and objective sleep outcomes (Gordon et al., 2020; O'Sullivan et al., 2023; Cunha et al., 2024; Herring and Meyer, 2024; Reid et al., 2010). These findings provide a strong rationale for lifestyle-based interventions aimed at enhancing well-being in young adults. Among the available exercise modalities, resistance training deserves particular attention. Beyond its musculoskeletal benefits, resistance training has shown potential to alleviate depressive and anxiety symptoms and improve sleep-related outcomes across populations (Gordon et al., 2020; O'Sullivan et al., 2023; Cunha et al., 2024; Herring and Meyer, 2024; Reid et al., 2010). Resistance training is also highly adaptable to supervised settings because exercise selection, external load, training volume, and progression can be prescribed and standardized with relative precision, making it both feasible and scalable in campus-based and novice populations, including young women.

However, the benefits of resistance training depend not only on participation but also on how the training stimulus is organized. In addition to frequency, intensity, and total volume, set structure is an important yet underexplored programming variable (Tufano et al., 2017). Traditional set configurations typically require repetitions or hold to be completed continuously until the prescribed work is achieved, which can induce substantial neuromuscular and perceptual fatigue (Izquierdo et al., 2006; Hooper et al., 2014; Gonzalez-Hernandez et al., 2020; Lea et al., 2022). This fatigue can increase perceived exertion, impair movement quality, and diminish the overall training experience, potentially hindering long-term adherence in sedentary individuals who have lower tolerance for fatiguing exercise (Gonzalez-Hernandez et al., 2020; Lea et al., 2022; Jukic et al., 2020; Yang et al., 2017; Teychenne et al., 2010; Zhai et al., 2015; Allen et al., 2019; Gao et al., 2023). Existing evidence further suggests that cluster-style methods may improve tolerability by attenuating acute fatigue, particularly in less-trained populations (Oliver et al., 2015; Dello Iacono et al., 2020; Boffey et al., 2021). We hypothesize that more frequent intra-set rest may reduce fatigue accumulation and sessional stress, reflected by lower perceived exertion and smaller cortisol perturbation, thereby improving recovery and subsequent sleep. Accordingly, any psychological benefit is expected to arise indirectly through altered internal load, recovery, and sleep-related stress regulation rather than from a unique psychiatric mechanism of cluster sets.

Current evidence suggests that resistance training can improve sleep and mental-health outcomes, and that cluster-set strategies may enhance exercise tolerability (Gordon et al., 2020; O'Sullivan et al., 2023; Cunha et al., 2024; Herring and Meyer, 2024; Reid et al., 2010; Jukic et al., 2020; Kredlow et al., 2015). Nevertheless, it is still unclear whether rest-redistribution cluster sets provide additional benefits for mental health and sleep outcomes beyond traditional sets when overall training content, load progression, and total rest time are matched. This question is especially evident in sedentary young women. Although recent evidence indicates that structured exercise interventions can improve sleep parameters in sedentary young women, direct comparisons of resistance training set structures are scarce (Zhang et al., 2025).

Therefore, the present randomized controlled trial has three aims. First, it will compare traditional resistance training and cluster-set resistance training with a non-exercising control condition to determine their effects on mental health and sleep outcomes in sedentary young women. Second, it will examine whether rest-redistribution cluster sets confer additional benefits over traditional sets when training content, load progression, and total rest time are matched. Third, it will explore changes following the 8-week intervention in maximal strength, body composition, and blood biomarkers to provide exploratory information on physiological responses.

## Methods

2

### Design

2.1

This single-blind, three-arm, parallel-group randomized controlled trial will be conducted at Beijing Sport University. The study aims to compare the effects of a non-exercising control condition (CON), traditional resistance training (TR), and rest-redistribution cluster-set resistance training (CS) on sleep quality and mental health in sedentary female college students. Outcome assessors will be blinded to group allocation. The study flowchart is shown in Figure 1.

**Figure 1 fig1:**
[figure not shown]
Flowchart of subject recruitment and study implementation.

### Participants

2.2

Participants will be sedentary female college students from universities in Beijing. They will be randomly assigned in a 1:1:1 ratio to CON, TR, or CS. We plan to enroll 48 participants (16 per group). The inclusion and exclusion criteria are as follows.

#### Inclusion criteria

2.2.1

Aged 18 to 24 years.No history of cardiovascular, hepatic, renal, or other major chronic diseases, and no current use within the past 3 months of medications that would contraindicate safe participation in resistance training.A sedentary lifestyle, defined as a daily sedentary time of >6 h and participation in moderate-intensity physical activity on fewer than 3 days per week (for at least 30 min per session) for over 3 months.Scores on the Depression, Anxiety and Stress Scales-21 Items (DASS-21) ≥ 44 (calculated by doubling the raw scores) (Lovibond and Lovibond, 1995).A Pittsburgh Sleep Quality Index (PSQI) global score of ≥ 7.0.

#### Exclusion criteria

2.2.2

An athlete or regular fitness enthusiast engaged in long-term resistance training.Inability to complete the full range of motion required by the intervention.Presence of any contraindication to exercise.

### Sample size estimation

2.3

Although the final efficacy analyses will use linear mixed-effects models, sample size was estimated at the design stage using the repeated-measures ANOVA interaction framework in G*Power as a pragmatic approximation for a three-group repeated-assessment trial. The primary outcomes for sample size calculations are DASS-21 scores and PSQI scores. Two-sided tests with effect size *f* = 0.25, *α* = 0.05, and power (1-*β*) = 80% were used with three groups and three measurements. The minimum total sample size required for the study was determined to be 36 participants after sample size calculation with repeated measures analysis of variance (between-group-within-group interaction) using G * Power Software (version 3.1.9.7) (Kang, 2021). Considering a potential dropout rate of 20–25% based on our previous similar studies, we decided to recruit 48 eligible young women.

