### Statistical analysis

2.12

All statistical analyses will be performed using SPSS version 26.0 and R software. Except for multiplicity-adjusted analyses of the co-primary outcomes, a two-sided *p*-value of <0.05 will be considered statistically significant. Continuous variables will be summarized as mean ± standard deviation (SD) if approximately normally distributed, or as median (interquartile range) otherwise. Categorical variables will be summarized as counts and percentages. Baseline characteristics will be described by group. The co-primary outcomes will be the DASS-21 total score and the PSQI total score.

The primary analysis will follow the intention-to-treat principle and will use linear mixed-effects models for repeated measures, given the longitudinal design and the possibility of incomplete follow-up (Krueger and Tian, 2004). For each continuous outcome, fixed effects will include group (CON, TR, and CS), time (Baseline, Week 4, and Week 8; treated as a categorical variable), and the group × time interaction, with participant included as a random effect to account for within-subject correlation across repeated assessments. For the co-primary outcomes, the primary inferential tests will focus on the group × time effects, with Holm-Bonferroni correction applied to control multiplicity across the two co-primary outcomes. For each co-primary outcome, the primary contrast will be the between-group difference in change from baseline to Week 8 estimated from the mixed-effects model. Prespecified pairwise comparisons among CON, TR, and CS, including CON versus TR, CON versus CS, and TR versus CS, will be conducted using model-estimated marginal means with adjustment for multiple comparisons. Analyses of Week 4 outcomes and secondary outcomes will be considered exploratory.

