Several limitations should be acknowledged. First, although the planned sample size was estimated for the co-primary outcomes, it remains limited. This trial is expected to detect moderate group-by-time interaction effects for the two co-primary outcomes, namely the DASS-21 total score and the PSQI global score, but may be underpowered to detect small effects in secondary outcomes, such as actigraphy-derived sleep parameters and blood biomarkers. Therefore, findings for secondary outcomes and biomarkers will be interpreted as exploratory, with emphasis placed on the direction and magnitude of estimated effects and their 95% confidence intervals rather than solely on statistical significance. Second, the 8-week intervention duration is sufficient to detect short-term changes but may not capture the long-term maintenance of benefits; future studies with extended follow-up are warranted. In addition, the actigraphy measures in this protocol are intended to characterize sleep continuity rather than polysomnographic sleep architecture, and the biomarker panel should be interpreted as exploratory because cortisol is strongly time-dependent and peripheral serotonin is sensitive to pre-analytical handling. Third, because this is a single-centre trial recruiting sedentary female college students from universities in Beijing, the findings may not generalize directly to men, non-student populations, other geographic or socioeconomic contexts, or women with different hormonal characteristics. Finally, although additional standardization and monitoring procedures have been introduced for factors such as caffeine exposure, menstrual-cycle phase, academic stress, and non-intervention physical activity, residual confounding cannot be fully excluded in this pragmatic field-based trial.

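### The 80% power covers one unadjusted group × time test; the Holm step and the week-8 pairwise contrasts, including TR versus CS, were not sized, and the limitations do not say so

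*Protocol article*

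**What the plan says.** Section 2.3 (Sample size estimation) gives the inputs: "Two-sided tests with effect size *f* = 0.25, *α* = 0.05, and power (1-*β*) = 80% were used with three groups and three measurements". The routine is "repeated measures analysis of variance (between-group-within-group interaction) using G * Power Software (version 3.1.9.7", and the result is "The minimum total sample size required for the study was determined to be 36 participants after sample size calculation". Recruitment is then raised for attrition: "Considering a potential dropout rate of 20–25% based on our previous similar studies, we decided to recruit 48 eligible young women". The section calls the ANOVA calculation a pragmatic stand-in for the mixed model.

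Section 2.12 (Statistical analysis) directs the primary inference at the group × time effects, "with Holm-Bonferroni correction applied to control multiplicity across the two co-primary outcomes". It then names, for each co-primary outcome, the between-group difference in change from baseline to week 8 as the primary contrast. It also prespecifies all three pairwise comparisons, TR versus CS among them, with a multiplicity adjustment.

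The Introduction makes TR versus CS the second of three aims. The limitations paragraph of the Discussion (section 3) says: "This trial is expected to detect moderate group-by-time interaction effects for the two co-primary outcomes". It calls the sample limited, but its specific warning about low power concerns small effects in secondary outcomes.

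**The concern.** The sized test and the planned inference are not the same. The calculation has one outcome, one α of 0.05 and one 4-df omnibus test. The analysis has two outcomes under Holm, a week-8 contrast, and three adjusted pairwise comparisons. An omnibus test can reach its power because both training arms differ from control, so its 80% carries no information about TR versus CS.

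This matters because the two training arms share exercises, loads and total rest, so a small TR–CS difference, and hence a non-significant result, is plausible. With the power caveat confined to secondary outcomes, a reader could take such a result on DASS-21 or PSQI as evidence against a moderate difference. The design cannot support that.

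**Working it through.** **Inputs.** From 2.3: f = 0.25, α = 0.05, three groups (k = 3), three measurements (m = 3), N = 36, recruit 48. From 2.12: Holm over two outcomes, so the smaller p-value is tested at 0.025; three pairwise comparisons. Assumed because not stated: correlation ρ = 0.5 and ε = 1, the values that reproduce 36.

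**1. The plan's own figure.** λ = f²·N·m/(1 − ρ), df1 = (k − 1)(m − 1) = 4, df2 = (N − k)(m − 1).
- N = 36: λ = 0.0625 × 36 × 3/0.5 = 13.5, df2 = 66, power 82.3%.
- N = 33: power 78.1%. So 36 is the smallest multiple of three.
- Attrition: 36/0.75 = 48.

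The stated arithmetic is right for that test.

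**2. First Holm step.** Same formula (ρ = 0.5):

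| Completers | α = 0.05 | α = 0.025 |
|---|---|---|
| 36 | 82.3% | 73.5% |
| 39 | 85.8% | 78.1% |
| 42 | 88.7% | 82.0% |
| 48 | 93.0% | 88.2% |

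If both outcomes truly have f = 0.25, a 20,000-run simulation at N = 36 gives per-outcome Holm power of 78–80% and power to win both of 67–73%, for outcome correlations from 0.8 down to 0 (per outcome) and 0 up to 0.8 (both).

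**3. Dependence on ρ at N = 36.**

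| ρ | α = 0.05 | α = 0.025 |
|---|---|---|
| 0.3 | 66.2% | 54.9% |
| 0.4 | 73.9% | 63.4% |
| 0.5 | 82.3% | 73.5% |
| 0.6 | 90.6% | 84.6% |
| 0.7 | 97.1% | 94.5% |

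**4. What f = 0.25 means here.** In this routine f² is the mean squared interaction effect over the nine cells, in units of the outcome variance. So the nine squared effects sum to 9 × 0.0625 = 0.5625, whatever ρ is. Let D be the week-8 difference between the extreme arms:
- TR = CS, linear over time: D²/3 = 0.5625, D = 1.30 SD.
- TR = CS, full effect by week 4: 4D²/9 = 0.5625, D = 1.13 SD.
- Arms evenly spaced, linear: D²/4 = 0.5625, D = 1.50 SD, so CS − TR = 0.75 SD.
- Arms evenly spaced, full effect by week 4: D²/3 = 0.5625, D = 1.30 SD, so CS − TR = 0.65 SD.

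The first two patterns reach the stated power with no TR–CS difference at all.

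**5. Pairwise week-8 contrasts.** Noncentral t with noncentrality (δ/SD of change)·√(n/2). At ρ = 0.5 the SD of change equals the outcome SD, since √(2 × 0.5) = 1. Ranges in the second and third columns come from taking error df as 3n − 3 or 2(3n − 3).

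| Per arm | Detectable at 80%, α = 0.05 | Detectable at 80%, α = 0.05/3 |
|---|---|---|
| 12 | 1.16–1.18 SD | 1.35–1.38 SD |
| 16 | 1.00–1.01 SD | 1.16–1.18 SD |

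For the CS − TR gaps of 0.65 and 0.75 SD in step 4, with 12 per arm and 3n − 3 df, power is 34% and 43% unadjusted, and 19% and 26% at 0.05/3. Raising ρ to 0.7 lifts the 0.75 SD unadjusted figure from 43% to 63%.

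**The case against.** A good deal can be said for the protocol, and most of it limits the point without removing it.

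- A reader might infer that the sample-size arithmetic is wrong. It is not: both 36 and 48 reproduce.
- A reader might infer that the sized test is absent from the confirmatory plan. It is not: 2.12 directs the primary inference at the group × time effects. The difficulty is that the same paragraph adds Holm and then names a different primary contrast.
- A reader might infer that the protocol claims 80% power for TR versus CS, or would treat a null result as equivalence. No sentence says either. The fault is that the caveat stops at secondary outcomes although TR versus CS is an aim and a prespecified comparison on the co-primary ones.
- The Holm loss is modest. The 74% needs attrition at the top of the stated range and only one responding outcome. With all 48 retained the first step has 88%, and the mixed model also uses partial data from dropouts, so counting completers is conservative.
- The unknown correlation cuts both ways, as the table shows. An article may leave that input to a fuller document; it matters here only because the stated power depends on it.
- f = 0.25 is conventionally moderate on its own scale. The conversion to SD units depends on the assumed mean pattern, but every pattern tried gives more than 1 SD.
- The first aim fares much better: for 1.13 to 1.50 SD, a training-versus-control contrast with 12 per arm has 77–95% power unadjusted and 60–87% at 0.05/3 (3n − 3 df).

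**Conclusion.** The point holds as a mismatch between what was sized and what will be tested, together with a limitations statement that is too broad. The 80% belongs to a single unadjusted omnibus test. At the first Holm step it becomes about 74% at 36 completers, 78% at 39 and 88% at 48, or about 78–80% per outcome at 36 if both outcomes respond. The larger gap is in the pairwise contrasts: only differences of about 1.2 SD of change (1.35 to 1.4 SD at 0.05/3) are detectable with 80% power at 12 per arm, and about 1.0 and 1.2 SD at 16 per arm. TR versus CS is therefore not covered by the power statement.

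These figures rest on ρ = 0.5 and ε = 1, except the 1.1 to 1.5 SD conversion, which does not depend on ρ. The 0.05/3 level is an assumed Bonferroni form of an adjustment that the article does not name. None of this shows that N = 48 is untenable or that TR versus CS should cease to be an aim.

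**What to change.** Keep N = 48 and all three aims.

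In 2.3:
- State that the 80% is for the group × time omnibus test at unadjusted 0.05.
- Give the correlation and ε that were used.
- Report power at the first Holm step across 36 to 48 completers (about 74% to 88% if ρ = 0.5).
- Report the week-8 pairwise difference detectable with 80% power at 12 and at 16 per arm.

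In the limitations paragraph of the Discussion:
- Replace the unqualified statement about moderate effects with the implied effect in SD units (about 1.1 to 1.5 outcome SD between the extreme arms).
- Extend the low-power caveat to TR versus CS on DASS-21 and PSQI.
- State that a non-significant TR-versus-CS result, reported with its 95% confidence interval, is not evidence of no difference.

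The cost is wording only, with no extra participants and no change to the analysis. The downside is that the published power figures become less favourable.

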### Recruitment

2.4

Sedentary female college students will be recruited from universities in Beijing through campus-wide advertisements and online announcements. Individuals expressing interest will first undergo a preliminary eligibility screening conducted by the research team. Those who meet the initial criteria will be invited to an on-site screening visit to further verify eligibility against the predefined inclusion and exclusion criteria.

Eligibility will be confirmed based on age (18–24 years), sedentary lifestyle characteristics, relevant medical history, and questionnaire-based thresholds, including a DASS-21 score ≥ 44 and a PSQI global score of ≥ 7.0. Exclusion criteria will be assessed concurrently, including long-term habitual resistance training (e.g., athletes or regular fitness enthusiasts), inability to complete the required range of motion, and any medical contraindication to exercise participation.

Prior to enrolment, eligible participants will receive a detailed explanation of the study procedures and will provide written informed consent. After completion of baseline assessments, participants will be randomly assigned in a 1:1:1 ratio to the non-exercising control group (CON), traditional resistance training (TR), or rest-redistribution cluster-set resistance training (CS). Recruitment will continue until the target sample size is achieved.

